#### *II.1.2. Patient Classification :*

Before statistical analysis, all the patient charts will be reviewed at 6 months follow up in order to ascertain the definite diagnosis of the nodule. This panel review will rassemble the 3 investigators and a radiologist from one of the center. Panel's analysis will include clinical, histological, radiological as well as any pertinent data on nodule characteristics that may prove to influence the diagnostic yield of the procedures (such as size, localisation, bronchus or vessel convergence sign)

#### *II.1.3. Alveoscopy sequences analysis*

Final detailed analysis of alveoscopy sequences will be performed at the Rouen University Hospital, by an independant observer, blindly from the histology results. For this purpose, several items will be analyzed and

coded such as general organisation of the elastin network, solid pattern, vascular network organisation after fluorescein IV injection, or any other items that would appear significant to differentiate benign from malignant lesions.

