**Experimental plan:**

Multicentric prospective controlled trial, conducted in three academic centers, specialized in interventional bronchoscopy, equipped with both navigational bronchoscopy and probe based confocal microendoscopy techniques.

120 subjects with peripheral lung nodule requiring navigational bronchoscopy will be included in the study and explored using both Confocal endoscopy AND navigational bronchoscopy. Confocal probe will be inserted in the same catheter as used for the navigational bronchoscopy and confocal images will be recorded before and after fluorescein IV injection, and before sampling.

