#### *II.1.1 Patients and procedures:*

Patients with peripheral lung nodule requiring biopsy sampling by navigational bronchoscopy (EBUS or EMN) will be recruited in three French centers : (Pr [name] - CHU de Rouen, Pr [name] - CHU de Saint Etienne, [name] - CHU de Toulouse). These three centers are currently equipped with EBUS , Electromagnetic navigation and probe based confocal microendoscopy (Cell Vizio)

During the procedure, at least one normal alveolar area will be imaged using pCLE on the same side than the peripheral lung nodule to serve as normal control. After a successful tentative of nodule localisation using navigational bronchoscopy, the cellvizio miniprobe will be introduced into the extended working channel for confocal in situ imaging. If confocal imaging fails to show a solid network pattern, a biopsy will be performed and the investigator will be authorized to move the navigational device ( EBUS or EMN) to another position, followed by another confocal imaging and biopsy. A maximum of three attempts to obtain a solid pattern using confocal will be authorized in each patient, after what the procedure will be considered as « failed ». When a solid confocal pattern is obtained, an IV injection of 5 ml fluoresceine sodium 1% will be performed for another imaging before biopsy sampling.

In each case, confocal images will be annotated with the precise identification of the biopsy performed, the images will be stored and a digital copy sent to the Rouen University Hospital for further analysis.

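### The central observer is masked to histology only, so fluorescein sequences can reveal the site's solid call and can inform the codes for pre-injection signs

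*Protocol*

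**What the plan says.** **When fluorescein is given.** Protocol II.1.1: "When a solid confocal pattern is obtained, an IV injection of 5 ml fluoresceine sodium 1% will be performed for another imaging". If no solid pattern appears, the path is a biopsy and a move of the navigational device, then renewed imaging. "A maximum of three attempts to obtain a solid pattern using confocal will be authorized in each patient", after which the procedure counts as failed. No injection is described on that path.

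**The same step in the opening summary and the synopsis.** Experimental plan: "confocal images will be recorded before and after fluorescein IV injection, and before sampling". No solid-pattern condition is attached there.

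**What is sent for central reading.** II.1.1: "confocal images will be annotated with the precise identification of the biopsy performed, the images will be stored and a digital copy sent" to Rouen.

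**What is coded, and under what masking.** II.1.3 lists items "coded such as general organisation of the elastin network, solid pattern, vascular network organisation after fluorescein IV injection", together with any others that may separate benign from malignant lesions. The coding is done "by an independant observer, blindly from the histology results". IV.6 repeats masking to histology, and to nothing else, for the patients who follow the initial description of signs.

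**What the codes feed.** The second of the Main assessment criteria is the set of predictive values of confocal signs for cancer, both without and with the injected fluorophore.

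**The concern.** Independent reading protects a result only if the reader cannot see the answer that the reading is meant to check. Here the protocol's own procedure places a marker of the operator's verdict in the image file, and the stated masking does not remove it. The operator makes the live call just after navigation is judged to have reached the nodule, so that call is not made naively. The central code is the only masked look at the same sign.

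Two things are at stake. The first is whether the central solid-pattern code says anything beyond what the site already said. The second is whether the signs coded before injection are really pre-injection results. If the observer has the post-injection images open, the before and after predictive values are no longer separate, and the gain from fluorescein cannot be read from their difference.

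**Working it through.** The point concerns masking, and the plan states no figure for it. The check sets the sections side by side.

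**Step 1. What a file tells its reader.** Under II.1.1 as written:

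| Content of the file | What it implies about the site |
|---|---|
| Post-fluorescein sequence present | operator called that position solid |
| No fluorescein, and a further position follows | operator called the earlier position not solid |
| Three positions, no fluorescein | procedure classed as failed |

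The site call can thus be inferred without any explicit annotation. This follows from II.1.1 describing no other route to an injection. The text does not expressly say that injection is given only in that case.

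**Step 2. What the masking covers.** II.1.3 and IV.6 name histology. Neither names the site call. Neither separates the solid-pattern and elastin items, which can be read before injection, from the vascular items, which need the injection.

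**Step 3. Which results depend on the central codes.**
- *Predictive values before and after injection* (Main assessment criteria, item 2; also III.2.2 and III.3.3). They rest on coded imaging signs, so they are exposed if post-injection images are seen during pre-injection coding.
- *Central solid-pattern code* (II.1.3). It is exposed through the cue in Step 1.
- *Primary count* (III.3.1). Positivity is a solid pattern seen in vivo plus a conclusive biopsy at one of the attempts. The hypotheses section likewise requires the pattern to be obtained in vivo, and II.1.1 declares failure during the procedure. All three point to the live call. No section lets the central code override it.

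**Step 4. Direction of the effect, on assumed values only.** Suppose a true solid pattern in 65% of cases, site and central reader each with sensitivity and specificity 0.9, and independent errors.
- Both solid: 0.65 × 0.9² + 0.35 × 0.1² = 0.530
- Neither solid: 0.65 × 0.1² + 0.35 × 0.9² = 0.290
- Each type of disagreement: 0.65 × 0.09 + 0.35 × 0.09 = 0.090
- Observed agreement 0.820; chance agreement 0.62² + 0.38² = 0.529
- Site-versus-central kappa = (0.820 − 0.529)/(1 − 0.529) = 0.62

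If the central reader adopts the site call in half of the disagreements, observed agreement is 0.910 and kappa is 0.81. If always, kappa is 1.0. With sensitivity and specificity each set at 0.8 or 0.9, kappa runs from 0.34 to 0.62 for independent reads and from 0.67 to 0.81 with half adopted. High agreement could then reflect copying rather than a clear sign. This kappa compares site with central reader. The value of 0.74 in the protocol compares confocal imaging with navigation and is not affected.

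**The case against.** A reader might infer that the primary verdict is at risk: 70/78 = 89.7% misses the 90% bar and 71/78 = 91.0% clears it, so one or two swayed central calls could decide the trial. The documents do not support this. The endpoint most naturally rests on the live call (Step 3), and no rule lets the central code change it. No disagreement rate is given from which to count movable calls. The threshold itself is not uniform either: the opening Experimental plan accepts 70 of 78, while the Statistical evaluation asks for 71.

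Further objections, and what remains of each:

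- *Histology is the right item to mask for benign versus malignant.* This stands. III.3.1 counts benign and malignant lesions alike as solid-positive, so the cue does not reveal the reference diagnosis.
- *Fluorescein imaging may be unconditional.* The opening summary and synopsis can be read so. If every patient had it, the cue to the site call would vanish, but the mixing of pre- and post-injection reading would remain.
- *Reading order belongs in a reading manual or the SAP.* Partly stands. Silence on order is not in itself an error, and the protocol does not say what the observer receives. But it does fix the scope of masking, twice, and the site call lies outside it.
- *The annotation identifies the biopsy only.* This stands. It is not said to record the solid call, nor to be shown to the observer. The inference in Step 1 does not need it.

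**Conclusion.** The concern holds as a gap in the reading procedure. With masking to histology alone, an observer given the full file can infer the site's solid call and can see post-injection images when coding pre-injection signs. The central solid-pattern code is then a weak check on the site, and the before-injection predictive values may carry post-injection information.

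The conclusion rests on two assumptions: that the conditional injection step in II.1.1 is what happens, and that the observer receives pre- and post-injection sequences together. The second harm needs only the latter. The documents cannot show that a reader would in fact be swayed, and they supply no figure from which to size the effect on the predictive values. The kappa values above show direction only. The primary count is not shown to move. This is a low-cost improvement, not a threat to the main conclusion.

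**What to change.** 1. In II.1.3, and for the confirmation step in IV.6, have the same observer read in two stages. First, code the pre-injection sequences alone, in random order, with fluorescein sequences, attempt number and biopsy annotation withheld, and lock those codes. Then release the post-fluorescein sequences and code the vascular items.
2. State that the observer is masked to the site call as well as to histology.
3. State in III.3.1 that the live call defines the primary criterion and that the central code is a check on it.
4. Reconcile the unconditional before-and-after wording of the Experimental plan with the conditional step in II.1.1. Which of the two is intended is for the sponsor to say.

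Cost: files must be prepared and each case is opened twice. The reader, the images and the patient procedure stay as they are. One limit remains: the joint description of signs by the three investigators in the first cases (IV.6) is not covered by this change.

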### **III. Research trial**

#### **III. 1. Hypotheses**

(a), pCLE has the same sensitivity than modern navigational endoscopic techniques such as EBUS or EMN for the diagnosis of peripheral lung nodules.

(b) pCLE is able to differentiate in vivo in real time malignant nodules from benign lesions.

#### **III.2. Objectives**

##### *III.2.1. Primary objective*

To determine if Alveoscopy can help to the localization and sampling of a peripheral lung nodule in vivo in showing a solid pattern.

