#### **III.3. Patient number, statistical analysis**

##### *III.3.1. Principal criteria analysis :*

In this study, we will consider that, to be valid for the diagnosis of peripheral nodule, alveoscopy should recognize 90% or more nodules that are successfully localized and sampled using navigational bronchoscopy techniques.

Positivity criteria for alveoscopy is defined as in-vivo imaging of a solid pattern and a conclusive biopsy sampling (benign or malignant) of the lesion during one of the navigational attempt to localize the lesion. Alveoscopy will be considered negative if a normal pattern is observed, with a conclusive biopsy of the nodule in the same location.

Navigational bronchoscopy results will be considered positive in case of conclusive biopsy at the first attempt of localisation of the lesion during bronchoscopy.

Therefore, there is a possibility that final results of the study show superiority of confocal imaging over navigational bronchoscopy , if pCLE allows for a better control and correction of the position of the navigational probe during the procedure.

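### The 90% pass rule counts only nodules with a conclusive first biopsy, so it cannot show that confocal imaging helps localisation and sampling, and it conflicts with the protocol's own count comparison and kappa

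*Protocol*

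**What the plan says.** The primary objective in III.2.1 is "To determine if Alveoscopy can help to the localization and sampling of a peripheral lung nodule in vivo in showing a solid pattern".

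III.3.1 then fixes the criterion:

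- Pass rule: "alveoscopy should recognize 90% or more nodules that are successfully localized and sampled using navigational bronchoscopy techniques". The synopsis (Statistical evaluation) puts this at 71 of 78, and the opening summary (Experimental plan) at 70 of 78.
- Navigation: "Navigational bronchoscopy results will be considered positive in case of conclusive biopsy at the first attempt of localisation of the lesion during bronchoscopy".
- pCLE positive: a solid pattern with "a conclusive biopsy sampling (benign or malignant) of the lesion during one of the navigational attempt to localize the lesion".
- pCLE negative: "Alveoscopy will be considered negative if a normal pattern is observed, with a conclusive biopsy of the nodule in the same location".

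III.3.1 closes by saying that pCLE could prove superior if it lets the operator correct the position of the navigational probe.

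On procedure, II.1.1 introduces the confocal probe after navigation has localised the nodule. "If confocal imaging fails to show a solid network pattern, a biopsy will be performed", and the navigational device may then be moved. "A maximum of three attempts to obtain a solid pattern using confocal will be authorized in each patient". Stored images are annotated with the biopsy they belong to.

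Other sections frame the comparison differently. Both lists of main assessment criteria compare the number of lesions localised by each technique, with no restriction to navigation-positives. Both statements of study objectives ask for non-inferiority in localisation. III.3.2 cites a paired non-inferiority test (Tango), 78 navigation-positive patients, a kappa of 0.74, 65% sensitivity and 120 patients in total.

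**The concern.** III.2.1 asks whether seeing a solid pattern helps to reach and sample the nodule. The pass rule asks how often the pattern is solid where navigation had already produced a conclusive first biopsy. In those patients sampling had succeeded. Help could appear only in patients whose first biopsy was inconclusive, and the rule leaves them out.

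The pCLE definitions do not repair this. Both the positive and the negative category require a conclusive biopsy. A solid pattern with an inconclusive biopsy (false reassurance) and a normal pattern with an inconclusive biopsy (a correct warning) have no category, yet both bear directly on whether the pattern helps.

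At stake is what a pass would mean. The trial could meet its 90% rule and be read as showing that pCLE aids sampling, although the rule cannot register such a benefit. Conversely, a real gain from repositioning would not count towards the pass rule.

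**Working it through.** **Inputs.** N = 120, navigation sensitivity 65%, 78 navigation-positives, kappa 0.74, alpha 5% (sidedness not given), power 80% (all III.3.2); pass mark 71/78 (synopsis) or 70/78 (opening summary). The 10% in III.3.2 is read here as a non-inferiority margin of 10 points.

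**1. The plan's figures.** 78/0.65 = 120, reproduced. 0.90 × 78 = 70.2, so at least 71 are needed: 71/78 = 91.0%, while 70/78 = 89.7% is below 90%. The two pass marks disagree by one patient.

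Discordance is not stated. Inferred from kappa 0.74 with both techniques at 65%, chance agreement is 0.65² + 0.35² = 0.545 and discordance is (1 − 0.74) × (1 − 0.545) = 11.8%. With true difference 0 and margin 0.10, exact power of the Tango test at n = 78 is 78.1% at one-sided 5%, close to the stated 80% (64.8% at one-sided 2.5%). This calculation needs both discordant cells: nodules lost by pCLE and nodules gained by it. Among 78 navigation-positives the gain cell is empty by definition.

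**2. Which population gives kappa 0.74?** Kappa = (observed − chance agreement)/(1 − chance agreement), with 71 agreeing positives and 7 losses:

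- Within the 78: observed = 71/78 and chance = 1 × 71/78, so kappa = 0.
- All 120, no gains: observed = (71 + 42)/120 = 0.942; chance = 0.65 × 0.592 + 0.35 × 0.408 = 0.5275; kappa = 0.88.
- All 120, 7 gains: observed = (71 + 35)/120 = 0.883; chance = 0.545; kappa = 0.744.

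With 70/78 the nearest value is 0.746, at 6 gains. The inferred discordance agrees: 0.1183 × 120 = 14.2 patients, about 7 losses and 7 gains. The stated kappa therefore presupposes nodules that the pass rule leaves out.

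**3. Does the pass rule respond to gains?** Hold 71/78 fixed and let c be the nodules gained among the 42 navigation-negatives (an assumption, range 0 to 21). Paired difference = (71 + c − 78)/120, with Tango 95% CI:

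| c | pass rule | pCLE vs navigation | difference, points (95% CI) |
|---|---|---|---|
| 0 | 91.0% | 71 vs 78 | −5.8 (−11.6 to −2.6) |
| 7 | 91.0% | 78 vs 78 | 0.0 (−6.7 to +6.7) |
| 14 | 91.0% | 85 vs 78 | +5.8 (−1.8 to +13.8) |
| 21 | 91.0% | 92 vs 78 | +11.7 (+3.2 to +20.5) |

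The pass rule does not move. The decision can differ too: at c = 0 the rule is met, but the lower limit lies beyond −10 points (−11.6 at 95%, −10.4 at 90%).

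**4. What a position-level comparison would separate.** This illustration covers first positions only and assumes all 120 are imaged, with 71 of the 78 conclusive positions solid.

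- Case A: 38 of the 42 inconclusive positions are also solid. Yield is 71/109 = 65% at solid and 7/11 = 64% at non-solid positions, so the pattern does not help.
- Case B: 4 of the 42 are solid. Yield is 71/75 = 95% against 7/45 = 16%, so the pattern is highly informative.

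The share of navigation-positives that are solid at the first position is 71/78 in both. The per-patient score could be higher, because a non-solid first position may be followed by a solid one.

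**The case against.** The strongest reply is that the 90% rule is not the whole primary analysis. The main assessment criteria compare lesion counts without restriction, III.3.1 credits pCLE at any attempt and mentions superiority, and III.3.2 names a paired test. All of this implies that navigation-negatives are counted. That stands, and it turns the point into a contradiction about the comparison population. A reader might infer that navigation-negatives are ignored throughout; the documents do not support that.

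A reader might also infer that the trial will return 71 of 78 whether pCLE helps or not. It will not: 71 (or 70) is a pass mark, and the observed share can fall anywhere up to 78/78. Only its insensitivity to gains is fixed.

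It can also be said that III.2.1 is loosely worded, and that the objectives and hypotheses elsewhere ask for non-inferiority or equal sensitivity, a question to which the 90% rule is relevant. This is fair, and recognising true nodules as solid is a necessary part of any help. It supports rewording III.2.1 but does not reconcile it with the rule.

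The hypotheses paragraph defines navigation-positivity without the first-attempt limit. Under that reading a nodule reached after repositioning could be credited to both techniques, so a gain would still not show.

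Two cautions stand. Because II.1.1 images after a successful localisation, some of the 42 may never be imaged, so the data for step 4 may be incomplete and its precision cannot be stated in advance. And pCLE has up to three attempts against one scored for navigation, so later gains mix a pCLE effect with plain repeat sampling.

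**Conclusion.** The point holds in this form: the pass rule in III.3.1 cannot answer III.2.1 and cannot show the superiority that III.3.1 itself foresees. It also conflicts with the main assessment criteria and with the kappa in III.3.2. Over an assumed 0 to 21 gains the paired difference shifts by 17.5 points (from −5.8 to +11.7) while the rule stays at 91.0%. The kappa result rests on a table of 120 patients with 78 navigation-positives and 71 recognised; the gains and the Case A and B splits are illustrative.

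This should be corrected because it is a mismatch between objective and criterion within the protocol, which any analysis plan would inherit.

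**What to change.** In III.3.1:

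1. State that the paired comparison covers all included patients, with navigation-negatives counted, and keep the 90% rule as a recognition criterion only. This needs no more patients: at the inferred 11.8% discordance and a true difference of 0, exact Tango power at 120 is 91.4% at one-sided 5% and 83.8% at one-sided 2.5%.
2. To answer III.2.1, compare the conclusive-biopsy rate at solid and non-solid imaged positions. Make first positions alone the main version, so that repeat sampling is not credited to pCLE. Give all positions, with a patient-clustered CI, as support.
3. Give solid pattern with inconclusive biopsy, and normal pattern with inconclusive biopsy, their own categories.
4. Report how many patients were never imaged.

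Alternatively, reword III.2.1 to match the non-inferiority question in the stated objectives and drop the superiority sentence. The comparison population must still be settled, and the pass mark given once.

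The cost is protocol wording and one further analysis. II.1.1 already provides for biopsies at solid and non-solid positions and ties images to biopsies, so no procedure or patient is added. The drawback is that precision depends on how many navigation-negative positions are imaged.

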##### *III.2.2. Secondary objectives*

- a. To determine Sensitivity, specificity, positive and negative predictive values of alveoscopy signs for the differentiation between benign and malignant nodules.
- b. To confirm the good tolerance of the technique

#### **III.3. Patient number, statistical analysis**

##### *III.3.1. Principal criteria analysis :*

In this study, we will consider that, to be valid for the diagnosis of peripheral nodule, alveoscopy should recognize 90% or more nodules that are successfully localized and sampled using navigational bronchoscopy techniques.

Positivity criteria for alveoscopy is defined as in-vivo imaging of a solid pattern and a conclusive biopsy sampling (benign or malignant) of the lesion during one of the navigational attempt to localize the lesion. Alveoscopy will be considered negative if a normal pattern is observed, with a conclusive biopsy of the nodule in the same location.

Navigational bronchoscopy results will be considered positive in case of conclusive biopsy at the first attempt of localisation of the lesion during bronchoscopy.

Therefore, there is a possibility that final results of the study show superiority of confocal imaging over navigational bronchoscopy , if pCLE allows for a better control and correction of the position of the navigational probe during the procedure.

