**Main assessment criteria:**

1. number of lesions localized by confocal endoscopy compared to navigational bronchoscopy
2. Positive and negative predictive values of confocal signs before and after IV fluorophore injection for the diagnosis of cancer.

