**Experimental plan:**

Multicentric prospective controlled trial, conducted in three academic centers, specialized in interventional bronchoscopy, equipped with both navigational bronchoscopy and probe based confocal microendoscopy techniques.

Subjects with peripheral lung nodule requiring navigational bronchoscopy will be included in the study and explored using both Confocal endoscopy AND navigational bronchoscopy. Confocal probe will be inserted in the same catheter as used for the navigational bronchoscopy and confocal images will be recorded before and after fluorescein IV injection, and before sampling.

In this study, positive diagnostic criteria for the localization of peripheral nodule using confocal imaging is a solid pattern as opposed to the usual loose fibered network pattern of the normal alveolar duct. According to this criteria, the confocal imaging procedure will be considered as valid if the number of lesions localized by confocal is not inferior to 90 % of those localized by navigational bronchoscopy. Therefore, pCLE will prove valid if it can recognize at least 70 subjects out of the 78 / 120 subjects for which the navigational bronchoscopy is forecasted to localize the peripheral lesion (Cohen concordance Kappa value of 0,74 between confocal and navigational bronchoscopy).

A secondary objective will be to describe specific signs of cancer using confocal endoscopy . This will be assessed on the first 30 patients using confocal imaging obtained before and after fluorophore IV injection, in comparison to histology, and confirmed on the following 48 patients.

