**Statistical evaluation :**

In this study, positive diagnostic criteria for the localization of peripheral nodule using confocal imaging is a solid pattern as opposed to the usual loose fibered network pattern of the normal alveolar duct. According to this criteria, the confocal imaging procedure will be considered as valid if the number of lesions recognized by confocal is not inferior to 90 % of those localized by navigational bronchoscopy. Therefore, pCLE will prove valid if it can recognize at least 71 of 78 nodules / subjects efficiently sampled using navigational bronchoscopy (Cohen concordance Kappa value of 0,74 between confocal and navigational bronchoscopy).

A secondary objective will be to describe specific signs of cancer using confocal endoscopy . This will be assessed on the first 30 patients (including 20 cancers) using confocal imaging obtained before and after fluorophore IV injection, in comparison to histology, and confirmed on the following 48 patients.

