### *III.3.2. Number of subjects.*

Because each patient is evaluated by both navigational bronchoscopy and confocal procedure, the required number of patient can be calculated based on a non-inferiority test for paired data. (Tango T. Equivalence test and confidence interval for the difference in proportions for the paired-sample design, Statistics in medicine 17, 891-908, 1998.) . According to this test, 78 patients positive for navigational bronchoscopy are needed to show a 10 % performance difference between the techniques (alpha risk 5%, Power 80%). This proportion corresponds to a 0,74 concordance using Cohen Kappa test. Forecasted sensitivity of navigational bronchoscopy being 65%, the total number of patients required for the study is 120.

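### The primary comparison is stated both as lesion counts per technique and as recognition among navigation-positive nodules; the count rule can pass where the recognition rule fails

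*Protocol*

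**What the plan says.** **Counts per technique.** Main criterion 1, in the opening summary and again in the synopsis, is the "number of lesions localized by confocal endoscopy compared to navigational bronchoscopy". The Experimental plan of the opening summary calls the procedure "valid if the number of lesions localized by confocal is not inferior to 90 % of those localized by navigational bronchoscopy". The synopsis, under Statistical evaluation, has nearly the same sentence.

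**Recognition among navigation-positive nodules.** Both of those paragraphs go straight on, with the word *therefore*, to a threshold on the 78: "at least 70 subjects out of the 78 / 120 subjects for which the navigational bronchoscopy is forecasted to localize the peripheral lesion" in the first and "at least 71 of 78 nodules / subjects efficiently sampled using navigational bronchoscopy" in the second. Section III.3.1 opens with a rule of the same kind: "alveoscopy should recognize 90% or more nodules that are successfully localized and sampled using navigational bronchoscopy techniques".

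**Superiority remark.** III.3.1 then counts pCLE as positive at any navigational attempt but navigation as positive only at the first, and infers that "there is a possibility that final results of the study show superiority of confocal imaging over navigational bronchoscopy".

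**Sample size.** III.3.2 cites Tango's paired non-inferiority test and says that "78 patients positive for navigational bronchoscopy are needed to show a 10 % performance difference between the techniques", at alpha 5% and power 80%. It links this to a kappa of 0.74 and reaches 120 patients from a forecast navigation sensitivity of 65%.

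**The concern.** The two wordings treat one group of patients differently: those in whom pCLE succeeds and navigation does not. Under the count wording, each such patient offsets a navigation-positive nodule that pCLE missed. Under the recognition wording, such patients are outside the denominator and every miss stands.

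III.3.1 contains both ideas. Its opening rule has a ceiling of 78 of 78, which is a tie with navigation, yet its last paragraph foresees superiority. III.3.2 sizes the study with a test and an agreement measure that need the pCLE-only group, but expresses the result as a number of navigation-positive patients.

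At stake is the meaning of a positive trial. By the count wording, pCLE could be called valid while missing more than 10% of the nodules that navigation finds, which the opening rule of III.3.1 says is not valid.

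**Working it through.** **1. Notation.** For the paired table let *a* = both positive, *b* = navigation only, *c* = pCLE only, *d* = neither.
- Recognition rule: a/(a+b) ≥ 0.90.
- Count rule: (a+c)/(a+b) ≥ 0.90.

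The second ratio exceeds the first by c/(a+b), which is never negative. So the count rule cannot fail when the recognition rule passes. The recognition ratio cannot exceed 1, so it cannot show superiority.

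**2. The plan's own figures.**
- Total: 78/0.65 = 120. Reproduced.
- Threshold: 0.90 × 78 = 70.2. Then 70/78 = 89.7% and 71/78 = 91.0%, so the two stated thresholds lie on either side of 90%.
- The 78: n = (z_alpha + z_power)² × ψ / margin², where ψ = (b+c)/n is the total discordance. The protocol gives neither ψ nor sidedness. With two-sided 5%, 80% power, margin 0.10 and an assumed ψ = 0.10, (1.96 + 0.842)² × 0.10/0.01 = 78.5, close to 78. The formula uses both discordant cells.
- Kappa on all 120, table 71/7/7/35: observed agreement 106/120 = 0.883; expected (78×78 + 42×42)/120² = 0.545; kappa = (0.883 − 0.545)/(1 − 0.545) = 0.744. This matches 0.74.
- The same table with no pCLE-only cases (71/7/0/42): kappa = 0.877.
- The 78 alone (71/7/0/0): observed and expected agreement are both 71/78, so kappa = 0.

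With 71 nodules recognised, the stated kappa is therefore reached on all 120 with 7 pCLE-only successes. The 71-of-78 rule does not count these.

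**3. Can the pCLE-only cell be filled?** Yes, under III.3.1: a non-conclusive first biopsy, followed by a solid pattern and a conclusive biopsy at a later attempt, is navigation-negative and pCLE-positive. II.1.1 allows up to three attempts. II.1.1 also places confocal imaging after a successful navigational localisation, which may keep the cell small.

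**4. Example (illustrative counts).** 78 navigation-positive, 42 negative; pCLE positive in 66 of the 78 and 8 of the 42.
- Recognition rule: 66/78 = 84.6%, fail.
- Count rule: (66 + 8)/78 = 94.9%, pass.

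**5. How often the verdicts differ.** Model: m ~ Bin(120, 0.65) navigation-positive; hits ~ Bin(m, 0.85); gains ~ Bin(120 − m, g). Recognition passes if hits ≥ 0.9m; count passes if hits + gains ≥ 0.9m. The 85% and g are assumptions.

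| g | Recognition passes | Count passes | Verdicts differ |
|---|---|---|---|
| 0% | 11% | 11% | 0% |
| 2% | 11% | 18% | 7% |
| 5% | 11% | 31% | 21% |
| 10% | 11% | 54% | 43% |
| 20% | 11% | 86% | 75% |

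Disagreement cannot exceed the chance that the recognition rule fails. That is 89% at 85% true recognition; the same model with 95% gives only 3%.

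**6. Thresholds against the paired test.** A result of 71/78 with no pCLE-only cases meets both point rules. Its Tango lower 95% limit is −11.5 points on 120 patients, or −17.4 points on the 78 alone, so a 10-point margin is not met either way. The power stated in III.3.2 therefore does not describe the 71-of-78 rule.

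**The case against.** The best counter-argument is that the protocol settles the matter itself. In the opening summary and the synopsis the count sentence leads directly into a threshold among navigation-positive subjects, and III.3.1 opens with the same rule. Every numeric threshold uses the 78. The main-criterion lines are short labels, and nowhere is a navigation-negative find said to offset a miss. This stands in part: recognition among navigation-positives is the better-supported reading. It does not explain why the superiority remark, the paired test and the kappa all need the cell which that reading leaves out.

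Some stronger readings are tempting but not supported:
- *That the trial plans a superiority claim.* The sentence is a remark. It sets no hypothesis, threshold or test, and cannot make the trial pass or fail.
- *That there are two margins, 12 and 7 fewer localisations.* A reader might take 10% of 120, but III.3.2 attaches its 10% to the 78 positive patients.
- *That the paired test also reverses the verdict in the example above.* On 120 patients it gives z = 1.70, which passes at one-sided 5% (1.645) and fails at one-sided 2.5% (1.96). Sidedness is not stated, so this shows nothing either way.
- *That the analyst is free to choose after seeing the data.* A statistical analysis plan may exist and fix the comparison; it was not available.
- *That conflict is frequent.* It vanishes if there are no pCLE-only cases, and the 71/7/7/35 table passes both rules.

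**Conclusion.** The inconsistency is real and lies in the current text. Lesion counts and recognition among navigation-positive nodules are both given as the primary comparison. The second has the numeric thresholds; the superiority remark, paired test and kappa fit only a comparison that includes pCLE-only cases.

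On the point rules the consequence has one direction, which favours the new technique: counts pass, recognition fails. Its frequency cannot be fixed from the protocol. It runs from 0 to 75% of trials for pCLE-only rates of 0 to 20% at an assumed true recognition of 85%, and is small if true recognition is well above 90% or the rate is near zero. The totals of 78 and 120 are not disproved. What needs correcting is the definition of the deciding comparison and the rule to which the power statement belongs.

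**What to change.** Name one deciding comparison and align with it main criterion 1 (both places), the Experimental plan in the opening summary, Statistical evaluation in the synopsis, III.3.1 and III.3.2.

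If it is the opening rule of III.3.1, the only one given numeric thresholds:
- use one threshold in place of 70 and 71;
- say whether it is a point rule or a test against 90%;
- state that superiority cannot be concluded from it;
- report the paired comparison on all 120 (both discordant cells, Tango interval, kappa) as secondary;
- reword III.3.2 so that its power statement is not attributed to the subset rule.

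**Cost.** No new data are needed for the rewording, but nodules found only by pCLE no longer count toward the primary claim. The choice between point rule and test also matters. As a point rule, 71 or more of 78 is met 48% of the time when true recognition is exactly 90%. As an exact one-sided 5% test against 90%, 75 of 78 are needed, with 45% power at 95% true recognition. If a test is chosen, the sample size must be justified again. If the all-120 paired comparison is chosen instead, the 70/71-of-78 thresholds should go, and III.3.2 should state the margin, sidedness and discordance on all 120.
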